## Abstract

**Background:**

Individuals receiving buprenorphine treatment for opioid use disorder (OUD) remain at high risk for treatment discontinuation and return to opioid use. Transcranial magnetic stimulation (TMS) has shown efficacy in reducing craving and substance use in other substance use disorders, but its application in OUD remains limited and the neural mechanism underlying its therapeutic effects is poorly understood. Determining the feasibility and generalizability of TMS in patients receiving buprenorphine – the most commonly prescribed medication for OUD – is therefore critical. This protocol aims to address these issues in a clinical trial of weekly TMS sessions for OUD.

**Methods:**

We will enroll up to 120 individuals with OUD taking buprenorphine in a randomized, single-blind, sham-controlled trial of left dorsolateral prefrontal cortex (DLPFC)-targeted intermittent theta burst stimulation (iTBS). Participants will receive active or sham iTBS weekly (2 sessions of 1800 pulses each applied once per week x 8 weeks, 16 sessions total) with pre- and post-iTBS assessments (10, 12, 20 weeks) of craving, opioid use, and treatment retention. A subset of individuals will undergo optional pre- and post-iTBS neuroimaging. The study will be conducted at an academic medical center and a private outpatient TMS clinic.

**Aims:**

Our primary aim is to determine whether 16 sessions of active iTBS applied to the left DLPFC results in reduced craving and opioid use, and higher treatment retention, relative to sham. In a secondary aim, we will also examine whether iTBS-related changes in craving are associated with changes in functional connectivity between the left DLPFC and both the dorsal striatum and anterior cingulate cortex.

**Discussion:**

By evaluating the feasibility and efficacy of a weekly TMS protocol that aligns with routine care and focuses on patients maintained on buprenorphine, this study addresses key limitations of prior TMS research in OUD. Furthermore, the inclusion of neuroimaging will help characterize the neural mechanisms underlying TMS-related changes in craving.

**Trial registration:**

This clinical trial is registered at ClinicalTrials.Gov; ID NCT07457489; date of registration: 03/02/2026.

## Introduction

Opioid use disorder (OUD) affects over 16 million people each year and remains the leading cause of fatal overdoses worldwide [1]. Gold-standard medications for the treatment of OUD, such as buprenorphine, the most widely prescribed medication for OUD [2], safely reduce mortality and drug use [3,4]. However, even with buprenorphine treatment, relapse and treatment discontinuation rates remain high for people with OUD; the three-month period after treatment initiation presents the highest risk for return to use [5,6]. Within 6 months of starting buprenorphine, only 50% of patients will continue treatment, and 91% will return to use [7]. Together, these data highlight the need for adjunctive treatments that address the drivers of return to use and treatment discontinuation.

Noninvasive brain stimulation has been explored as a treatment for substance use disorders (SUDs), including OUD. Transcranial magnetic stimulation (TMS) is one form of noninvasive brain stimulation that uses electromagnetic pulses to modulate cortical excitability and induce neuroplastic changes [8,9]. The U.S. Food and Drug Administration (FDA) has cleared TMS for the treatment of depression, obsessive-compulsive disorder and for smoking cessation [10] with clinical protocols typically administering stimulation over the dorsolateral prefrontal cortex (DLPFC) [11]. Within these applications, intermittent theta burst stimulation (iTBS), a specific type of patterned TMS, has demonstrated significant clinical utility. iTBS is thought to increase synaptic long-term potentiation by enhancing cortical excitability [12,13]. Crucially, reviews and meta-analyses across multiple SUDs have shown that TMS (including iTBS) is effective at reducing craving and substance use [14–16]. It is hypothesized that TMS exerts therapeutic effects by targeting the neural circuits that contribute to drug craving and seeking [17].

Despite these promising findings, research examining TMS in OUD remains limited, with reviews of noninvasive brain stimulation in OUD identifying only a handful of studies [18–20]. Existing studies of TMS for OUD primarily focus on individuals using heroin and only one study has assessed the impact of accelerated deep TMS in people receiving buprenorphine for OUD [21]. To date, only four studies have investigated TMS for OUD in North America – where the use of the highly potent synthetic opioid, fentanyl, has been steadily increasing and presents a higher risk of overdose than heroin [22]. Two of these studies have used single-session TMS protocols to modulate craving or cognition [23,24]. One recently published study evaluated an accelerated TMS protocol in which 4 sessions of iTBS were delivered in a single day to a small sample of patients with OUD who were stable on their maintenance medications [25]. The authors reported reduced attentional bias to opioid cues, however this did not reach statistical significance. The third study implemented a repeated-sessions clinical protocol with TMS administered daily over multiple weeks [26]. However, of 87 individuals screened for participation, only 6 were randomized, and 4 completed the study. Accordingly, no statistical analyses were conducted on this small sample, thus limiting the evaluation of clinical efficacy and treatment outcomes. Notably, none of these studies evaluated individuals taking buprenorphine, despite it being the most commonly prescribed medication for OUD in North America [2]. As such, the following questions remain about the use of TMS for OUD:

Is TMS for OUD effective, and if so, how does it exert its effects? Only one study of TMS for OUD has included neuroimaging [24], despite neuroimaging being critical for helping to characterize the neural circuit changes that occur with TMS treatment.Is a weekly dosing schedule of TMS for OUD a feasible and acceptable adjunctive treatment? A previous study [26] testing therapeutic TMS protocols (i.e., daily sessions of treatment over multiple weeks) struggled with recruitment and retention, questioning the feasibility and acceptability of this intervention for this population.Can we provide TMS for populations with OUD beyond urban academic medical centers? Expanding access to TMS has been a challenge for the field more broadly, besides the treatment of SUDs. While clinical trials for TMS are typically conducted in academic medical centers, more widespread clinical application would ultimately require delivery of TMS for SUDs in private outpatient clinics nationwide.

To address these questions, we designed a multi-site randomized controlled trial of TMS for OUD among individuals receiving buprenorphine treatment. We will implement a novel weekly stimulation protocol designed to improve treatment efficiency and better align TMS delivery with routine weekly clinic visits. The trial will be conducted across both an academic medical center and private practice clinics throughout Tennessee to help address the question of clinical applicability beyond academic medical settings. Our central hypothesis is that DLPFC-targeted iTBS will significantly reduce both opioid craving and opioid use. In secondary analyses, we will use neuroimaging (MRI) to assess whether a change in functional connectivity between the DLPFC and both the dorsal striatum and anterior cingulate cortex (ACC) is associated with reductions in craving. Ultimately, this work aims to establish a safe and effective adjunctive therapy to directly mitigate the severe craving and high relapse rates that limit current OUD treatments.

## Methods

### Study design

The study is a randomized, single-blind, sham controlled clinical trial of iTBS to reduce opioid craving in people diagnosed with OUD who are currently receiving treatment with buprenorphine. The study consists of 12 study visits. Participants will also have the option to elect to participate in optional MRI scans before and after the intervention. At the first visit (Consent), participants will complete informed consent, which will be obtained by the researcher conducting the study. After completing consent, participants will undergo additional screening procedures to ensure safety to receive TMS (and safety to receive MRI if the participant elects to complete these scans) and will complete questionnaires (listed in Fig 1) about substance use and psychiatric symptoms. Enrolled participants will then undergo 8 weekly sessions of left DLPFC-targeted iTBS. Prior to the first TMS visit, individuals will be randomized to receive active or sham iTBS. At each TMS visit, participants will complete questionnaires about their substance use and psychiatric symptoms and provide a sample for urine toxicology. After the 8-week TMS intervention, participants will return for follow-up visits at weeks 10, 12, and 20. At each follow-up visit, participants will complete questionnaires about their substance use and psychiatric symptoms and provide a sample for urine toxicology. If a participant elects to undergo the optional MRI visits, they will undergo 2 MRI scans 1) before the first TMS visit; and 2) after the week 8 TMS visit. During both MRI scans, participants will complete a resting state fMRI and perform a task assessing cue reactivity in the scanner. At these sessions, participants will also complete tasks outside the scanner assessing inhibitory control and reward processing. See Figs 2 and 3 for a visualization of the study design and Fig 1 for a list of assessments conducted on each study visit. This protocol was developed with input from multiple certified peer recovery specialists ([name], [name], [name]), who are coauthors on this manuscript and have lived experience with substance use.

**Fig 1 pone.0357402.g001:**
[figure not shown]
Participant timeline: Schedule of enrollment, interventions, and assessments. *If participant elects to undergo MRI. **If a participant reports a history of bipolar disorder or screens positive on the DSM Screener. ***If able to become pregnant. BAM: Brief Addiction Monitor; BDI: Beck Depression Inventory; BPI: Brief Pain Inventory; MRI: Magnetic Resonance Imaging; OCS: Opioid Craving Scale; PCL5: PTSD Checklist for DSM-5; SCID: Structured Clinical Interview for DSM-5; SOWS: Subjective Opiate Withdrawal Scale; STAI: State-Trait Anxiety Inventory; TMS: Transcranial Magnetic Stimulation; TLFB: Timeline Follow Back; TRQ: Time to Relapse Questionnaire.

**Fig 2 pone.0357402.g002:**
[figure not shown]
Study Protocol Diagram. After consent and randomization to receive active or sham stimulation, participants will receive iTBS weekly (2 sessions once per week x 8 weeks) with pre- and post-intervention assessments of craving, opioid use, and treatment retention. RMT: resting motor threshold.

**Fig 3 pone.0357402.g003:**
[figure not shown]
Diagram of schedule of assessments. Participants will complete assessments of opioid use, treatment engagement and retention, drug use, craving and other psychiatric assessments before and after receiving TMS treatment. A subset of participants will also complete an optional neuroimaging session at baseline and post-TMS where measures of craving and cognition will be collected.

### Study approval and registration

This protocol is approved by the Vanderbilt University Medical Center (VUMC) Institutional Review Board (IRB) and Advarra IRB (VUMC Protocol ID: 251293; Advarra Protocol ID: Pro00094328). Modifications to the protocol (at both sites) will be communicated to the study teams by electronic notification (e.g., email). The protocol has also been registered at ClinicalTrials.gov (ID: NCT07457489). Results from this trial will be reported in ClinicalTrials.gov and will be published in academic journals. Results may also be disseminated at academic and medical conferences.

### Study setting

The study will include two enrolling sites, one of which is a medical academic institution (VUMC) and the other a private psychiatric clinic (SynapticPSYCH). Both sites have experience conducting research using TMS methods. Research ethics approval for the academic institution is covered by an institutional IRB. Research ethics approval for the clinic site is covered by an external central IRB. Protocol amendments will be submitted to the institutional IRB and external central IRB, which will send electronic notifications or changes required directly to the participating sites.

### Inclusion and exclusion criteria

*Inclusion*
*criteria*

Age between 18–65 yearsDiagnosis of OUD according to DSM-5 criteria and confirmed by SCID [27]Currently prescribed buprenorphine for opioid use disorderMeets either of the following criteria: (1) reports opioid craving of 2 or greater on a 0–10 scale, or (2) has returned to opioid use at least once within the past 12 monthsMust be able to read, speak and understand EnglishMust be judged by study staff to be capable of completing the study proceduresParticipants will be in stable outpatient psychiatric treatment and psychiatrically stable.

*Exclusion*
*criteria*

DSM-5 intellectual disabilitySubstance use disorder (other than opioid, nicotine, or cannabis) within the past 3 monthsCurrent, active suicidal ideation with intent or planPositive urine drug screen for illicit substance use that can increase seizure risk (cocaine, benzodiazepines, amphetamine, methamphetamine)History of psychosis in the past 3 months or diagnosis of a primary psychotic disorderAny history of a progressive or genetic neurologic disorder (e.g. Parkinson’s disease, multiple sclerosis, tuberous sclerosis, Alzheimer’s Disease) or acquired neurological disease (e.g., stroke, traumatic brain injury, tumor), including intracranial lesionsHistory of head trauma resulting in any loss of consciousness (>15 minutes) or neurological sequelaeCurrent history of poorly controlled headaches including chronic medication for migraine preventionHistory of fainting spells of unknown or undetermined etiology that might constitute seizuresHistory of seizures, diagnosis of epilepsy, or immediate (1st degree relative) family history epilepsy with the exception of a single seizure of benign etiology (e.g., febrile seizures) in the judgment of a board-certified neurologistChronic uncontrolled medical conditions that may cause a medical emergency in case of a provoked seizure (e.g., cardiac malformation, cardiac dysrhythmia, asthma, etc.)Any metal in the brain or skull (excluding dental fillings) or elsewhere in the body unless cleared by the responsible covering physician (e.g., MRI compatible joint replacement)Any devices such as pacemaker, medication pump, nerve stimulator, TENS unit, ventriculo-peritoneal shunt unless cleared by the responsible covering physicianAll female participants of child-bearing age will be required to have a pregnancy test; any participant who is pregnant or planning to become pregnant will not be enrolled in the studyMedications will be reviewed by the responsible covering physician and a decision about inclusion will be made based on the participant’s past medical history, drug dose, history of recent medication changes or duration of treatment, and use of CNS active drugs. The published TMS guidelines review of medications to be considered with TMS will be taken into consideration given their described effects on cortical excitability measuresParticipants who, in the investigator’s opinion, might not be suitable for the study or would be unable to tolerate the study visit

### Sample size

We plan to recruit up to 60 participants at each site (VUMC and SynpaticPSYCH) to obtain a completion sample of n = 50 at each site for a total of n = 100. With 80% power, a type 1 error rate of 5%, and 100 subjects across all sites, we can detect effect sizes larger than 0.40. Based on these calculations, our proposed total sample of n = 100 will provide adequate power to detect changes in craving and opioid use.

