### Statistical analysis plan

#### Primary outcome analysis.

A change in craving score (Δcraving) on the OCS will be calculated between pre-TMS (week 1 timepoint) and post-TMS (week 10 timepoint) and a linear model will determine whether Δcraving significantly differs between active and sham conditions (controlling for age, sex, and pre-TMS craving). Change in number of days of use on the TLFB (Δuse) will be calculated between pre-TMS (week 1 timepoint) and post-TMS (week 10 timepoint) and a model will determine whether Δuse significantly differs between active and sham conditions (controlling for age, sex, and pre-TMS days of use). In post hoc analyses, we will investigate the effects of buprenorphine dose in response to TMS.

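### The stated detectable effect of 0.40 does not hold for active versus sham: 100 completers detect about 0.57 unadjusted, and power at 0.40 is about 51%, not 80%

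*Protocol article*

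**What the plan says.** The Sample size section sets the numbers: "We plan to recruit up to 60 participants at each site", in order "to obtain a completion sample of n = 50 at each site for a total of n = 100". It then gives the power statement: at 80% power and a 5% type 1 error rate, with "100 subjects across all sites, we can detect effect sizes larger than 0.40". From this it concludes that "our proposed total sample of n = 100 will provide adequate power to detect changes in craving and opioid use". It does not name the effect-size metric, the test, the sidedness, the SD used as standardiser or a correlation between baseline and follow-up.

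Two other sections fix which comparison the figure must serve. Under Randomization and blinding procedures, participants are allocated within site by permuted blocks so that the groups stay balanced. Under Primary outcome analysis, the change in craving from week 1 to week 10 is tested for whether it "significantly differs between active and sham conditions (controlling for age, sex, and pre-TMS craving"), and change in days of opioid use is tested the same way with its own baseline value. Both primary tests are therefore between-arm contrasts.

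**The concern.** A total of 100 in two balanced arms is about 50 per arm, and 0.40 is too small a detectable difference for that size. It is the value expected from 100 per arm, or from a one-sample or paired test on 50 people. Neither is the planned primary analysis.

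This is the only quantitative justification of the sample size in the article, and it is used for both primary outcomes. If the true effect is 0.40 and adjustment gains little, the trial would miss it about half the time. A reader who trusted the printed 80% would then take a null result as fairly strong evidence against an effect of that size, which it would not be.

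**Working it through.** **Inputs**
- From Sample size: 5% type 1 error, 80% power, 100 completers in total, up to 120 recruited, detectable effect 0.40.
- Assumed: two-sided test; 1:1 allocation (the article says balanced, without a ratio), so n = 50 per arm; 0.40 read as a standardised mean difference d.

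**1. Attempt to reproduce 0.40, unadjusted**

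Normal approximation: d = (1.960 + 0.842) × √(2/50) = 2.802 × 0.200 = 0.560. The exact noncentral t calculation gives 0.566. The stated 0.40 is not reproduced.

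**2. Power at d = 0.40**

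Normal approximation: Φ(0.40/0.200 − 1.960) = Φ(0.040) = 51.6%. Noncentral t: 50.8%.

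**3. Size needed for 80% power at 0.40**

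n per arm = 2 × 2.802² / 0.40² = 98.1, so 99; noncentral t gives 99.08, so 100. That is about 200 completers, or 200 × 120/100 = 240 recruited at the article's own completion rate.

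**4. Other readings (noncentral t, 80% power)**

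| Reading | Detectable effect | Power at 0.40 |
|---|---|---|
| Two-sided, 50 per arm | 0.566 | 51% |
| One-sided, 50 per arm | 0.501 | 63% |
| Two-sided, 60 per arm (all 120 analysed) | 0.516 | 58% |
| Two-sided, 100 per arm | 0.398 | 80% |
| One-sample or paired, n = 50 | 0.404 | – |
| One-sample or paired, n = 100 | 0.283 | – |
| Cohen's f, two groups, N = 100 | 0.283 | – |
| Correlation, N = 100 | 0.277 | – |

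Only 100 per arm and the paired test on 50 give about 0.40. The article does not say that either was used.

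**5. Allowing for baseline adjustment**

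With correlation r between baseline and week 10, the residual SD is the raw SD times √(1 − r²). The detectable effect in raw-score SD units is then 0.566 × √(1 − r²). The few degrees of freedom spent on covariates are negligible here.

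| r | Detectable effect | Power at 0.40 |
|---|---|---|
| 0 | 0.566 | 51% |
| 0.3 | 0.54 | 55% |
| 0.5 | 0.49 | 63% |
| 0.6 | 0.45 | 70% |
| 0.7 | 0.404 | 79% |

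Setting 0.566 × √(1 − r²) = 0.40 gives r = √(1 − (0.40/0.566)²) = 0.71, that is, baseline explaining half the variance.

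**6. If the standardiser is the SD of the change score**

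With equal SDs at both times, the change-score SD is the raw SD times √(2(1 − r)). The detectable effect becomes 0.566 × √((1 + r)/2): 0.46 at r = 0.3, 0.49 at 0.5, 0.51 at 0.6 and 0.52 at 0.7. It equals 0.40 only at r = 0. On this scale a higher correlation makes the stated figure harder to reach.

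**The case against.** The best defence is that 0.57 and 51% describe an unadjusted test, whereas the planned model adjusts for baseline, age and sex. In raw-score SD units they are therefore the least favourable case. The central hypothesis is also directional, the section does not state sidedness, and up to 120 may be recruited. Combining these lowers the correlation needed for 0.40: to 0.60 with a one-sided test and 50 per arm, to 0.63 with a two-sided test and 60 per arm, and to 0.48 with a one-sided test and 60 per arm. A journal article may also leave the correlation and SD to the full protocol. Finally, the source of 0.40 is unknown: 100 per arm fits as well as a paired test on 50.

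Parts of this stand. The unadjusted figure must carry its conditions, and where 0.40 came from is inference only. But each rescue needs at least one assumption that the article does not make, and some need two or three. The section rests its calculation on 100 subjects, not 120, and multiple imputation would not restore the information of 120 complete records. The finding is not that detail is missing. The article prints a specific result, draws a conclusion from it, and its own printed inputs do not give that result for its own primary contrast.

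**Conclusion.** The stated figure is wrong as written and must be corrected. For a two-sided 5% test, 1:1 allocation and 100 analysed, the between-arm difference detectable with 80% power is 0.57 unadjusted and 0.45 to 0.54 with baseline adjustment at correlations of 0.6 down to 0.3 (raw-score SD units). Power at 0.40 is 51% unadjusted and 55% to 70% over that range of correlations. It reaches 80% only at a correlation of about 0.71. The conclusion that 100 completers give adequate power has no support from the number offered for it.

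As context only: if alpha were split equally over the two primary outcomes (0.025 each), the unadjusted detectable effect would be 0.62 and power at 0.40 would be 39%. The finding does not depend on this.

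**What to change.** Restate the Sample size section along these lines: with 50 completers per arm, the trial has 80% power (two-sided 5%) for a between-arm standardised difference of 0.57 unadjusted, or 0.49 with baseline adjustment if the baseline-to-week-10 correlation is 0.5. The 0.5 is an illustration, and the sponsor should put in the value it can support. Name the test, the sidedness, the SD used as standardiser and the assumed correlation. Remove 0.40 unless a correlation of at least 0.71 is justified, or the different assumptions that would support it are stated and defended. Reword the adequacy sentence to match the corrected figure.

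Do not carry the same figure over to opioid use. Days of use in the preceding week is a count from 0 to 7 and needs its own power statement.

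The cost is a wording change and a less favourable printed figure. No extra participants are needed to correct the statement. If the sponsor does need to detect 0.40, the question becomes one of sample size: about 99 to 100 completers per arm without adjustment, fewer with a supported correlation. Recruitment is projected to run to June 2028, so either decision can be made well before analysis.
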